### Trial objectives

#### Primary objective

The primary objective is to investigate whether in vitro anti-HLA T & B cell responses in sensitised patients can be inhibited by adoptive transfer of Tregs.

#### Secondary objectives:

Determine the proportion of sensitised dialysis patients who may be eligible for a future trial based on patterns of IFNγ/IL-17A responses to HLA on FluoroSpot, i.e. the proportion of patients with unregulated T & B cell anti-HLA responsesDetermine the duration of suppression of HLA-specific FluoroSpots by Tregs.Determine what adverse events associate with Treg therapy.

The secondary exploratory mechanistic objectives are:4-Determine how adoptive Treg therapy changes the number and phenotype of circulating Tregs comparing baseline to post-Treg treatment.5-Determine how adoptive Treg therapy changes HLA Ab profiles measured by Luminex.

##### Patient and public involvement

Members of the local Kidney Patients Association reviewed parts of the grant application to the Medical Research Council and provided feedback on how it could be improved. They were particularly helpful in ensuring the lay summary was written in a helpful way. A patient representative has been invited into the Trial Steering Committee. The findings of the study will be publicised in the Kidney Patients Association Newsletter, website and Facebook.

### Expected duration of trial

The end of the trial is defined as database lock (following completion of monitoring of the last patient last visit undergoing the GAMECHANgER-1 trial).

### Trial endpoints

Primary endpoints.

The primary endpoint is to determine the proportion of patients showing suppression of a defined HLA-specific IFNγ/IL-17A dual FluoroSpot response for 2 months post-treatment, compared to the proportion of patients who show the same changes during baseline immune monitoring. The production of only one cytokine (the one positive at enrolment) will need to be suppressed.

Secondary endpoints.

The secondary endpoints are:Proportion of sensitised dialysis patients with unregulated T & B cell anti-HLA responses, identified in Part 1 observations.Duration of suppression of HLA-specific responses by Tregs.Adverse events associated with Treg therapy.The secondary exploratory mechanistic endpoints are:4.Changes in Treg number and phenotype comparing baseline to post-Treg treatment, studied using detailed immunophenotyping performed by flow (and in selected samples where possible mass cytometry) using validated panels and protocols. Correlations between Treg numbers / phenotype and immune reactivity will be sought.5.The changes in HLA Ab profiles measured by Luminex beads will be assessed using samples taken at enrolment to the observational phase in all, then week 1, 4, 8 then 6- & 12-months post-treatment in those receiving Tregs and baseline, week 1, 4, 8 in those undergoing baseline immune monitoring. All time points ± 1 dialysis session with blood taken at the beginning of dialysis.

### Trial procedures (see Table 1)

**Table 1 Tab1:** Study Flow Sheet—Summary of trial procedures

	**Part 1 (Visit 1&2 ** ***n*** ** = 100: Visit 3–7 ** ***n*** ** = 9)**								**Part 2 (Stage 1 ** ***n*** ** = 12; Stage 2 ** ***n*** ** = 9)**							
Assessment	Visit 1	Visit 2	Visit 3	Visit 4	Visit 5	Visit 6	Visit 7	Pre-Part 2 eligibility re-check	Visit 1 leukapheresis	Visit 2 Treg infusion	Visit 3	Visit 4	Visit 5	Visit 6	Visit 7	Visit 8
Visit windows Part 1—Relative to Visit 3	See below			+ 1 week ± 1 dialysis session	+ 2 weeks ± 1 dialysis session	+ 4 weeks ± 1 dialysis session	+ 8 weeks ± 2 dialysis sessions	Within 2 weeks of visit 1 Part 2								
Visit windows Part 2—Relative to Visit 2									See below	See below	+ 1 week ± 1 dialysis session	+ 2 weeks ± 1 dialysis session	+ 4 weeks ± 1 dialysis session	+ 8 weeks ± 2 dialysis sessions	+ 6 months ± 3 dialysis sessions	+ 12 months ± 3 dialysis sessions
**Part 1 (** ***n*** ** = 100)**																
Registration Form & Consent	x															
Check / Re-check Inclusion/Exclusion Criteria	x							x								
Post-consent eligibility tests in some recruits*																
HIV, HepBSAg, HepC	x															
Liver function tests	x							x								
ECG	x							x								
Pregnancy test	x							x								
Medical and transplant history, including route of HLA sensitisation	x							x								
Record / update demographic data	x							x								
Blood sample for in vitro dual Fluorospot (in all)	x															
Inform patient of Fluorospot pattern (End of study if ineligible for Part 2)		x														
Baseline Immune monitoring (in first 9 recruits with fluorospot pattern eligible for Part 2) (*n* = 9)			x	x	x	x	x									
Physical exam								x								
Vital signs: pulse, temperature, BP			x	x	x	x	x	x								
Monitoring of AE and IME related to study procedures (i.e. blood test)		x	x	x	x	x	x	x								
**Part 2 (Stage 1 ** ***n*** ** = 12; Stage 2 ** ***n*** ** = 9)**																
Leukapheresis									x							
Symptoms-directed physical exam†									x	x	x	x	x	x	x	x
Vital signs: pulse, temperature, BP									x	x	x	x	x	x	x	x
Blood tests according to EU Tissues and Cells Directive #									x							
Treatment Immune monitoring										x	x	x	x	x	x	x
Full blood count, U&E, LFTs, CRP§										x	x	x	x	x	x	x
Record Concomitant medication										x	x	x	x	x	x	x
Monitoring of AE and IME related to study procedures									x							
Full AE and IME monitoring starts at time of TR001 infusion										x	x	x	x	x	x	x
Pregnancy test																x

Part 1

Visit 1 – At time of recruitment, or next convenient dialysis session if additional post-consent eligibility tests need doing. (Fluorospot only)

Visit 2 – Once visit 1 fluorospot results available No blood tests

Visit 3 – Week ‘0’. Once conditions to proceed with baseline immune monitoring have been met (see Sect. 7.1) (Fluorospot, HLA Ab, Treg numbers and phenotype) –

Visit 4 – 1 week after visit 3 ± 1 dialysis session (Fluorospot, HLA Ab, Treg numbers and phenotype)

Visit 5 – 2 weeks after visit 3 ± 1 dialysis session (Fluorospot only)

Visit 6 – 4 weeks after week 0 ± 1 dialysis session (Fluorospot, HLA Ab, Treg numbers and phenotype)

Visit 7 – 8 weeks after week 0 ± 2 dialysis sessions (Fluorospot, HLA Ab, Treg numbers and phenotype)

Pre-Part 2 eligibility re-check – to be performed approximately 2 weeks prior to leukapheresis

Part 2

Visit 1 – Leukapheresis – at a time convenient for the patient

Visit 2 – Treg infusion – at a time convenient for the patient once Tregs are ready – blood for Fluorospot assay, HLA Ab and determination of Treg numbers and phenotype taken pre-Treg infusion – Sample may be taken at the dialysis session before Treg infusion

Visit 3 – 1 week after Treg infusion ± 1 dialysis session (Fluorospot, HLA Ab, Treg numbers and phenotype)

Visit 4 – 2 weeks after Treg infusion ± 1 dialysis session (Fluorospot)

Visit 5 – 4 weeks after Treg infusion ± 1 dialysis session (Fluorospot, HLA Ab, Treg numbers and phenotype)

Visit 6 – 8 weeks after Treg infusion ± 2 dialysis sessions (Fluorospot, HLA Ab, Treg numbers and phenotype)

Visit 7 – 6 months after Treg infusion ± 3 dialysis sessions (Fluorospot, HLA Ab)

Visit 8 – 12 months after Treg infusion ± 3 dialysis sessions (Fluorospot, HLA Ab)

^*^ Post-consent eligibility tests in some recruits—Take HIV, HepBSAg, Hep C in all unless negative test results are available in last 5 years. Take LFTs in all unless results are available in last 3 months. Do ECG unless a SOC ECG within the last 3 months is available for review. Do pregnancy test on all women of child-bearing potential

^*^ Repeat eligibility tests in some patients at pre-Part 2 assessment. Take LFTs in all unless results are available in last 3 months. Do ECG unless a SOC ECG within the last 3 months is available for review. Do pregnancy test on all women of child-bearing potential

^†^ In all the post-TR001 infusion visits, the need for a symptoms-directed physical examination and/or symptom-specific tests will be determined according to standard medical care

^#^ Mandatory serological tests (Anti-HIV-1, 2, HBsAg, Anti HBc, Anti-HCV-Ab, *T. pallidum-*specific test) are supplemented with HTLV-I/II antibody testing. Window for performing is within 7 days after leukapheresis

^§^ Send sample for FBC, U&E, LFTs and CRP at every visit, unless results available from a dialysis session within the visit window

Visit Schedule and immune monitoring tests

Blood samples will be collected, processed and stored as previously published [13–15]. IFNγ/ IL-17A dual FluoroSpots will be used to describe the patterns of responsiveness to soluble HLA molecules (Pure HLA Proteins®). This assay will be performed on samples from all time points. HLA Ab profiles will be analysed by Luminex. This assay will be performed on samples from all time points except Week 2 of baseline immune monitoring, and Week 2 post-Treg infusion. Flow cytometry (and in selected samples mass cytometry) will be used to analyse phenotypes of circulating Tregs. This will be performed at selected time points. All non-routine laboratory assays will be performed according to Standard Operating Procedures (SOPs).

The Dual Fluoropsot assay will be the FluoroSpot^FLEX^ human IFNγ/ IL-17A dual colour FluoroSpot assay, for simultaneous assessment of both cytokines produced by human CD8-depleted PBMC after incubation with selected sHLA from Pure Protein. Absolute Treg numbers and phenotype will be analysed according to standard flow cytometric protocols in the Core facilities of Guy's Hospital Biomedical Research Centre. Where possible, and dependent on flow cytometry results, selected samples will be tested by mass cytometry in the same facility. The assays to determine HLA Ab profiles will be the LABScreen mixed beads for Class I and II antibody detection, followed by LABScreen single antigen HLA Class I and Class II beads for antibody definition (One Lambda, CA), which will then be analysed on the xMAP Luminex platform. This will be performed at the Viapath Clinical Transplantation Laboratory of Guy’s Hospital using validated protocols.

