### Exclusion criteria

The exclusion criteria for Part 1 are defined as follows:1) Living donor kidney transplant planned.2) Listed as recipient of multi-organ transplants (i.e. combined kidney and pancreas).3) Known Human Immunodeficiency virus (HIV) + or previous Hepatitis C Virus (HCV) or Hepatitis B Virus (HBV). If no HIV, HCV or HBV tests within 5 years, these will be performed post-consent.4) Patient involved in other clinical trials of investigational medicinal products (IMPs).5) Active infection or history of recurrent infection. Recurrent infection defined as more than 2 confirmed infections requiring either antibiotics, antivirals, antifungals or hospitalisation in 6 months prior to consent.6) Female patients of childbearing potential with a positive pregnancy test at enrolment.7) Female patients who are breastfeeding.8) Hypersensitivity to IMP or to any of the excipients.9) Known contraindication to the protocol-specified treatments or procedures.10) Severe liver impairment, defined as ≥ Grade 3 or severely elevated ALT, AST or total bilirubin, on bloods done within the last 3 months.11) Electrocardiogram (ECG) abnormalities suggesting active myocardial ischaemia or (potentially) malignant ventricular arrhythmia: ECG to have been performed within the last 3 months.12) Patients, who in the opinion of the PI, have a medical condition, or other relevant psychological, familial or social factor that may jeopardise their health, compliance, or influence the trial integrity in any way.

Exclusion criteria 1 and 4–12 will be re-checked at a screening visit prior to patient entering Part 2.

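### Table 1 schedules no pregnancy test between the re-check before leukapheresis and the Treg infusion, and sets no maximum for that interval

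*Protocol article*

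**What the plan says.** The eligibility re-check before Part 2 is placed relative to leukapheresis in two places. The window row of Table 1 puts it "Within 2 weeks of visit 1 Part 2", and the visit list below the table has it "to be performed approximately 2 weeks prior to leukapheresis". The Exclusion criteria section adds: "Exclusion criteria 1 and 4–12 will be re-checked at a screening visit prior to patient entering Part 2". That range includes criterion 6, on pregnancy. The Table 1 footnote on the re-check states "Do pregnancy test on all women of child-bearing potential".

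The infusion (Part 2 Visit 2) takes place "at a time convenient for the patient once Tregs are ready". Its cell in the window row only points down to the visit list, and the list gives no number of days or weeks.

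The Part 2 block of Table 1 has its own pregnancy-test row. Its single mark is in the Visit 8 column, and Visit 8 is "12 months after Treg infusion ± 3 dialysis sessions".

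The Inclusion criteria require willingness to use highly effective contraception to the end of follow-up, and ask for this to be reconfirmed before Part 2.

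**The concern.** The product exposure begins with the infusion, not with the leukapheresis. Table 1 recognises this, since full adverse-event monitoring starts at the infusion. The last pregnancy test, however, is tied to the leukapheresis, and the time between the two events is left open. A site that followed the printed schedule exactly would dose a woman of childbearing potential on a result obtained before her cells were even collected.

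What is at stake is the safety of a participant, and possibly of a fetus, at the trial's single dosing event. The trial's statistics are not affected.

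**Working it through.** The plan gives no figure on this point, so the check is a reading of the schedule.

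**Step 1. Where the tests fall.** Table 1 has 7 Part 1 visits, 1 re-check and 8 Part 2 visits: 7 + 1 + 8 = 16 columns. Pregnancy tests are marked in three of them:

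| Point in the schedule | Pregnancy test marked |
|---|---|
| Part 1 Visit 1 | yes |
| Pre-Part 2 re-check | yes |
| Part 2 Visit 1 (leukapheresis) | no |
| Part 2 Visit 2 (infusion) | no |
| Part 2 Visits 3 to 7 | no |
| Part 2 Visit 8 (12 months) | yes |

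Within Part 2 this is 1 of 8 visits. From the end of the re-check up to and including the infusion there are two visits and no test.

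**Step 2. How old the result is at infusion.** Let L be the time from re-check to leukapheresis and X the time from leukapheresis to infusion.

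Age of result at infusion = L + X

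- L is up to about 2 weeks (Table 1 window row and visit list).
- X covers isolation, expansion, quality control and cryopreservation (sections on the IMP and on Treg acquisition, expansion and administration), plus scheduling to suit the patient. The article gives neither a value nor a maximum for X.

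The schedule therefore sets no upper limit on L + X. No number of weeks is put on it here, because any such number would be assumed.

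**Step 3. Does the document itself treat an older result as good enough?** At the re-check, the Table 1 footnote accepts liver function tests and an ECG from the previous 3 months. It makes no such allowance for pregnancy: the test is done in every woman of childbearing potential, although she was already tested in Part 1. The authors thus want a current result on entry to Part 2, but the schedule does not carry that requirement forward to the day of dosing.

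**Step 4. Can a test be fitted in?** Visit 2 already has "blood for Fluorospot assay, HLA Ab and determination of Treg numbers and phenotype taken pre-Treg infusion", and "Sample may be taken at the dialysis session before Treg infusion". A sample before infusion therefore exists, and the earlier of the two options leaves time for a result.

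**The case against.** The strongest reply is that the article condenses a longer protocol. Table 1 is labelled a summary, the visit list refers to a section that is not reproduced, and a test before infusion may well be written there. Pregnancy risk is also already managed: highly effective contraception is an entry condition, it is reconfirmed for Part 2, and a test is done shortly before leukapheresis. Nothing in the endpoint, the error rates or the analysis depends on the point.

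Much of this stands. Contraception lowers the risk, the full protocol may contain the test, and the statistics are untouched. Condensation does not dispose of the point, however. The article does not leave pregnancy testing out. It prints the row and places the marks, and the dosing visit is left blank. The contraception commitment is not a test, and the document itself does not rely on it alone at the re-check.

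A reader might go further and infer that Visit 2 lacks patient safety checks, or that the product could be thawed before the examination, CRP and liver function tests had been looked at. The article does not support that. Visit 2 carries a symptom-led examination, vital signs, blood count, U&E, liver function tests, CRP and concomitant medication, and a consultant or similarly qualified practitioner gives the infusion. Rules for proceeding on the day commonly sit in the full protocol, so their absence here shows nothing. Exclusion criterion 10 accepts liver results up to 3 months old, and no eligibility criterion uses CRP.

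**Conclusion.** The point holds as a scheduling gap. As printed, the last pregnancy result before dosing predates leukapheresis, no test is marked at leukapheresis or infusion, and the interval to infusion has no maximum. The next test comes 12 months after infusion. Over that open interval the only stated protection against an unrecognised pregnancy is the contraception commitment.

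The size cannot be expressed as a rate. The article gives neither the time from leukapheresis to infusion nor the number of women of childbearing potential among the 21 patients to be treated. The conclusion rests on Table 1, its footnotes and the visit list as reproduced. If the full protocol has a test before infusion, what remains is a mismatch in the published schedule.

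This is a cheap safety improvement that should be made. It is not a flaw in the trial's design, and it does not touch the endpoint, alpha or power.

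**What to change.** Mark a pregnancy test for women of childbearing potential in the Part 2 Visit 2 column of Table 1. State in the Visit 2 entry that the sample may be drawn at that visit or at the preceding dialysis session, and that a negative result is required before infusion. If the full protocol already requires this, bring Table 1 into line with it.

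The cost is one inexpensive test per woman concerned, at a visit where blood is already taken, and an occasional short deferral while a result is awaited. A cryopreserved product allows for that deferral.

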### Description of the IMP

The Treg product, known as TR001 is classified as an Advanced Therapy IMP (ATIMP). It consists of autologous Tregs isolated from the peripheral blood of recruits by leukapheresis, polyclonally expanded ex vivo, then administered as a single use named patient therapy via intravenous infusion. Cells will be subjected to quality control assessments (immunophenotyping, sterility testing, mycoplasma, endotoxin, and viability) before use. The cell dose is 5–10 × 10^6^ cells/kg.

### Treg acquisition, expansion and administration

Treg acquisition and expansion

We have developed a GMP-compliant manufacturing process for the production of functionally suppressive TR001 [7]. Autologous PBMC are acquired by leukapheresis. Initial Treg isolation from PBMC consists of depletion of CD8^+^ T cells followed by enrichment for CD25^+^ T cells to obtain a CD4^+^CD25^+^ T cell population, which is subsequently expanded to provide sufficient cell yield. Tregs will be polyclonally expanded based on previous published and validated protocols [8–11, 16–20] in the presence of anti-CD3/CD28 beads, rapamycin (sirolimus) and the growth factor interleukin-2 (IL-2). The Tregs products will follow the same quality control steps prior to release as for the ONE study [10] and described in [8], ie ≥ 60% of CD4
^+^CD25^+^FOXP3^+^ cells and > 80% suppressive ability in a polyclonal suppression assay. The post-infusion immunological outcomes in UK patients enrolled in the ONE study have been published [11]. We will administer 5–10 × 10^6^ cells/kg, as this was the highest dose safely administered to similar patients in the ONE study [10] without adverse effects and is the dose that has been authorised for use by the TWO Study [21]. Only autologous Treg cells will be utilized in the study participants enrolled in the current trial.Treg administration

The TR001 will remain cryopreserved throughout the delivery steps. The cell product will be thawed at the bedside by appropriately trained staff and delivered by syringe into 50mls 4.5% sterile isotonic human serum albumin contained in a glass bottle or proprietary transfer bag. The final dispersed cell product (100mls) will then be infused intravenously by pump by a consultant or similarly qualified medical practitioner. It is anticipated that the infusion will take approximately 30 min.

### Statistical considerations and analysis

#### Sample Size calculation

Based on our previous experience of numbers of patients presenting anti-donor reactivity without evidence of suppression by CD25^+^ T cells, we have calculated that 100 patients will need to be recruited for Part 1. This number is based on availability of the clinical population in the study sites which is feasible in the study timeframe. For Part 2, Simon’s two-stage design will be used for the trial, with α = 0.05 and 1-β = 90%. Clinical consensus amongst the expert team is that if fewer than 20% meet the primary endpoint there is no merit in further investigating Tregs, whereas if ≥ 50% respond to Tregs further investigation will be merited. Based on these parameters, 21 patients are required, all of whom will be monitored for at least 2 months post-treatment to meet the data collection for the primary endpoint. Of these 21 patients, 12 will be allocated to stage 1 and 9 to stage 2, based on the order of recruitment. At the end of stage 1, data will be assessed for futility using stopping rules based on the clinical consensus: ≥ 6 patients meeting the primary endpoint, stage 2 will commence; ≤ 2 patients meeting the primary endpoint, the trial will stop; 3–5 patients meeting the primary endpoint, the trial will pause for the sample size to be re-estimated after discussion with the funder.

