**Methods:**

The aim of this trial is to determine whether adoptive transfer of autologous Tregs into HLA sensitised patients can suppress memory T and B cell responses against specific HLA antigens. This is a two-part, multi-centre, prospective clinical trial, comprising an observational phase (Part 1) aiming to identify patients with unregulated cellular memory responses to HLA (Pure HLA Proteins) followed by an interventional phase (Part 2). The first 9 patients identified as being eligible in Part 1 will undergo baseline immune monitoring for 2 months to inform statistical analysis of the primary endpoint. Part 2 is an adaptive, open labelled trial based on Simon’s two-stage design, with 21 patients receiving Good Manufacturing Practice (GMP)-grade polyclonally expanded Tregs to a dose of 5–10 × 106 cells/kg body weight. The primary EP is suppression of in vitro memory responses for 2 months post-infusion. 12 patients will receive treatment in stage 1 of Part 2, and 9 patients will receive treatment in stage 2 of Part 2 if ≥ 50% patients pass the primary EP in stage 1.

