**Fig. 1 Fig1:**
[figure not shown]
Trial Flow chart Part 1 Observational study: Identification of patients eligible for Part 2, based on pattern of IFNg/IL-17 reactivity on FluoroSpot assay. Some patients may have already had these assays performed in 2020 as part of an observational study (REC ref 16/WM/0370). Additional patients (up to n = 100) will be recruited and have blood withdrawn for testing to determine HLA-specific patterns of responsiveness in FluoroSpot assays, to identify those eligible for Treg therapy in Part 2, and to determine the size of the population for our proposed follow-on trial (beyond this study). All patients with either positive IL-17 or IFN gamma anti-HLA reactivity without evidence of regulation by CD25 + cells will be eligible to enter Part 2. The first 9 patients identified as being eligible, from any site, will undergo baseline immune monitoring for two months to inform statistical analysis of primary endpoint. If < 21 patients with Fluorospot patterns eligible for inclusion in Part 2 are identified, the study will terminate early. Part 2 Interventional Study: This is a two stage, adaptive, open labelled, trial based on Simon’s two stage design, with 12 patients treated in Part 2 Stage 1 and 9 treated in Part 2 Stage 2. Because of an expected high withdrawal rate, all patients recruited to Part 1 will consent to inclusion in Part 2. If more than 21 eligible patients are identified, the statisticians will draw up an algorithm at the end of milestone 1 to determine which patients are included in Part 2, to ensure that eligible patients from each of the three sites are included in a ratio proportionate to the number found eligible from each site. For instance, if after 75 patients have been analysed in Part 1, the number found eligible at each site is 15 (site 1), 10 (site 2) and 10 (site 3), then 9 from site 1 will be included, and 6 each from sites 2 and 3. The order of Treg dosing will be determined by the order in which eligibility for Part 2 was determined. Treg dosing: The exact number in Part 2 Stage 2 who receive Tregs will be determined by the results from Part 2 Stage 1, according to Simon’s 2 stage design. If fewer than 2 of the 12 in stage 1 reach primary endpoint (suppression of anti-HLA responses for at least two months post treatment), the trial will be stopped, concluding that Treg therapy has no efficacy. If 6 or more of the 12 in group 1 reach primary endpoint, we will proceed with dosing all 9 in stage 2. In the event that 3, 4 or 5 of the 12 patients in stage 1 respond, the estimates of efficacy are below our hoped for 50% but are not so low as to be regarded as evidence of futility. We will therefore pause the trial and re-estimate the number of patients that we need to recruit, after discussion with the funders. We anticipate withdrawals from both Part 1 and Part 2, for various reasons including transplantation, and so will likely enrol more than 21 patients to Part2

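### N = 21 and 90% power come from a Simon design that continues at 3 or more of 12, but the written rule pauses at 3–5, so the 90% holds only on conditions the protocol does not state

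*Protocol article*

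**What the plan says.** The Sample Size calculation section of the protocol article states that "Simon’s two-stage design will be used for the trial, with α = 0.05 and 1-β = 90" per cent. It sets the two response rates by clinical consensus: "if fewer than 20% meet the primary endpoint there is no merit in further investigating Tregs", while if at least half "respond to Tregs further investigation will be merited". It then concludes: "Based on these parameters, 21 patients are required", split 12 and 9.

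The same section gives three outcomes for stage 1, also attributed to clinical consensus. Six or more responders start stage 2, two or fewer end the trial, and in between "3–5 patients meeting the primary endpoint, the trial will pause for the sample size to be re-estimated after discussion with the funder".

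The other places that state the rule do not all agree:

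- The Abstract (Methods) says that "9 patients will receive treatment in stage 2 of Part 2 if ≥ 50% patients pass the primary EP in stage 1". It mentions no pause.
- The last paragraph of the Background gives the same condition as a count of six, again with no pause.
- The Fig. 1 legend attributes the stage 2 numbers to Simon's design and includes the pause, because at 3, 4 or 5 responders "the estimates of efficacy are below our hoped for 50% but are not so low as to be regarded as evidence of futility". It stops the trial only below 2 responders, so exactly 2 of 12 has no assigned outcome there.

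**The concern.** Simon's design has two outcomes at the interim look: stop or continue. Its 90% power is calculated on the footing that every trial above the stopping boundary is carried on to the full sample. The protocol keeps that design's sample size, stage sizes, alpha and power, but replaces its continuation rule.

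The replacement uses the target rate of 50% as a threshold for the observed stage 1 rate. In the design that gives 21, 50% is the true rate under the alternative. Overall success there needs only 8 of 21 (38.1%), and 3–5 of 12 (25% to 41.7%) is an ordinary stage 1 result when the true rate is 50%.

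At stake is what the trial can be said to deliver. A therapy that meets the target has more than a one-in-three chance of landing where the article fixes neither the next sample size nor the test, and where the decision follows a discussion held once the stage 1 count is known.

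**Working it through.** **Inputs** (Sample Size calculation section): p0 = 0.20, p1 = 0.50, alpha 0.05, power 0.90, n1 = 12, n2 = 9. Assumption: alpha is one-sided, as is usual for this design; the article does not say.

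**1. Reproduce the plan's figure.** An exact search over two-stage designs gives the minimax design: stop at 2 or fewer of 12, otherwise treat 21, success at 8 or more of 21. With X ~ Bin(12, p) and Y ~ Bin(9, p),

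P(success | p) = Σ (x = 3 to 12) P(X = x) · P(Y ≥ 8 − x).

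This is 0.0421 at p = 0.20 and 0.9010 at p = 0.50. The plan's 12 + 9 = 21 is reproduced exactly. Other settings give other totals: the optimal (rather than minimax) design needs 22, alpha 0.025 needs 26 (minimax), and 80% power needs 17 (minimax).

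**2. Apply the written stage 1 rule.**

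| True rate | Stop (≤ 2) | Pause (3–5) | Go (≥ 6) |
|---|---|---|---|
| 0.2 | 55.8% | 42.2% | 1.9% |
| 0.3 | 25.3% | 62.9% | 11.8% |
| 0.4 | 8.3% | 58.2% | 33.5% |
| 0.5 | 1.9% | 36.8% | 61.3% |

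**3. Split the 90.1% by stage 1 result (p = 0.50).**

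| Responders of 12 | P(X = x) | P(Y ≥ 8 − x) | Product |
|---|---|---|---|
| 3 | 0.0537 | 0.5000 | 0.0269 |
| 4 | 0.1208 | 0.7461 | 0.0902 |
| 5 | 0.1934 | 0.9102 | 0.1760 |
| 3–5 together | 0.3679 | – | 0.2930 |
| 6 or more | 0.6128 | – | 0.6080 |

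The total is 0.2930 + 0.6080 = 0.9010. The route without a pause supplies 60.8%. Whatever final cut-off is used, that route cannot exceed P(X ≥ 6) = 61.3%.

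**4. Power under different fates of a paused trial (p = 0.50).**

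- None resumes: 0.608.
- All resume to 21, success at 8 or more: 0.901.
- All resume to a larger total with an ordinary exact test at 0.05: 0.935 (N = 25), 0.939 (N = 30), 0.970 (N = 40), 0.976 (N = 60).
- Upper bound, every paused trial ends in success: 0.608 + 0.368 = 0.976.

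**5. Conditional error at p = 0.20.** P(Y ≥ 8 − x) is 0.020, 0.086 and 0.262 for x = 3, 4 and 5. These are the levels at which stage 2 can be tested after a change of N without exceeding Simon's overall alpha of 0.042.

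**6. Type I error if N is re-chosen without adjustment.** Take, for each count, the least favourable total N from 21 to 60 with an exact test at 0.05. The conditional errors become 0.0437, 0.1057 and 0.2618. Then 0.0122 + 0.2362 × 0.0437 + 0.1329 × 0.1057 + 0.0532 × 0.2618 = 0.0505.

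**7. The disagreement at exactly 2 responders.** At p = 0.20, P(X ≤ 2) − P(X ≤ 1) = 0.5583 − 0.2749 = 0.283, so this is a likely result for an ineffective therapy. It barely affects the error rates: stopping at 1 or fewer, with the rest as in Simon's design, gives alpha 0.0430 and power 0.9051.

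**The case against.** The strongest objection is that a pause is not a failure. The Fig. 1 legend says that 3–5 responders is not evidence of futility and that the number to recruit will be re-estimated, so the stated intention leans towards resuming. If paused trials resume to 21 or more under a sensible test, power is 90% or higher in the cases calculated in step 4. This stands. A reader might infer that the trial has 61% power, but the documents do not support that: 60.8% is the extreme in which no paused trial resumes.

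A reader might also take the 50% figure as a success threshold at the end of the trial. The text does not say so. It pairs 50% with 20% as the parameters from which 21 is derived, which makes it the design alternative. Nor is the absence of a final cut-off out of 21 a fault here, because the full protocol or the SAP may give it, and part of the re-estimation method may sit there too. Sight of the data adds no separate complaint: Part 2 is open-label with one arm. Type I error is secondary, since even the unadjusted worst case in step 6 is only marginally above 0.05.

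Finally, the analysis is described as mainly descriptive, with confidence intervals, in a phase IIa trial, and the pause is a deliberate consensus choice. That limits the consequences. It does not make the power statement correct, because the article makes the statement and also sets out a rule that does not produce it.

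**Conclusion.** The point holds in a limited form. N = 21 is right for the stated inputs, but the 90% power belongs to a design that continues at 3 or more of 12, which is not the rule the protocol writes down. At a true rate of 50%, 36.8% of trials enter the pause zone, and 29.3 of the 90.1 points of power depend on what happens there. The 90% at N = 21 holds only if every paused trial resumes to 21 under Simon's cut-off. It is 60.8% if none resumes, and undetermined otherwise.

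The Abstract and Background are stricter still: read alone, they make stage 2 conditional on 6 or more and leave no route for 3–5.

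The figures assume one-sided alpha and, except for the 61.3% ceiling and the stage 1 probabilities, success at 8 or more of 21. That cut-off comes from the search, not from the article.

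**What to change.** Before stage 1 results are seen, choose one of the following:

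- **(a)** Adopt the statistical rule that N = 21 assumes: 3 or more of 12 goes on to the remaining 9, with success at 8 or more of 21 (alpha 0.042, power 0.901).
- **(b)** Keep the funder discussion at 3–5, but pre-specify that total N is at least 21 and that stage 2 is tested at Simon's conditional error (0.020, 0.086 and 0.262 for 3, 4 and 5 responders). Fix the permitted values of N in a table, because the exact test moves in steps. With 3 responders and 10 further patients, 5 of 10 has probability 0.033 at p = 0.20, above 0.020, so 6 of 10 are needed. The chance of success at p = 0.50 is then 0.377, against 0.500 with 9 further patients.
- **(c)** Keep the pause as written, but state that 90% applies only if paused trials resume to 21 under Simon's cut-off, and that the path without a pause has about 61% power.

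In each case, make the Abstract, Background, Fig. 1 legend and Sample Size calculation section give the same rule. This includes the stop boundary, which is below 2 in the legend and 2 or fewer in the sample size section.

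The cost is wording in the protocol and SAP. No option needs more than the planned 21 patients unless the sponsor chooses to extend under (b) or (c). The downside is that the sponsor commits in advance to a rule at 3–5 responders, or publishes a less favourable power.
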